### Data collection

Both the intervention and control groups will complete demographic questions and two brief questionnaires (pre and post intervention). Demographic information includes: age, area of residence, education, marital status, whether a current smoker, and country of birth. This data will be collected via the Cool Runnings app. Any identifiable information about participants will be stored on a secure, password-protected, encrypted server by the platform licensor (iPug Pty Ltd), and only de-identified information will be passed on to the study investigator. The Licensing Agreement contains a confidentiality clause that states that no information will be released by the licensor to any third parties.

### Primary outcome measure

The primary outcome measure is change in knowledge. Change in knowledge is measured in three components. The first component is knowledge of correct burn first aid. This is measured by an open-ended question (see Table 1). Correct burn first aid knowledge is defined as cool running water for 20 min or more. This is based on clinical evidence of benefit [20, 21]. Any other response reflects incorrect knowledge. The second component is knowledge of the main cause of burns/scalds in children aged 0–15 years (Table 1). This is assessed via response to a multiple-choice question. Any response other than ‘hot drinks’ is coded as incorrect. The third component is knowledge about the main age group at risk for burns/scalds (Table 1). This is also assessed via a multiple-choice question. Any response other than ‘0–2 years’ is coded as incorrect. As such, each of these variables is recoded into dichotomous variable (correct/incorrect). The proportion of correct responses to each of these three knowledge variables will be measured at baseline and post intervention (6 months) using pre and post questionnaires specifically designed for this study [21].

**Table 1 Tab1:** Outcome measures from pre and post intervention questionnaires for Cool Runnings

Primary outcome questions	Answer options
Hot beverage scald risk:	
What do you think is the main cause of burns and/or scalds in children aged 0–15 years in Australia?	• Bath/taps • Heaters • Hot drinks • Camp fires • Kettle/stovetops • Hair-straighteners • Oven doors • BBQs
What age group do you think is most at risk of receiving this type of burn/scald injury?	• Under 2 years • 2–5 years • 6–10 years • 11–15 years
Burn first-aid treatment:	
What is the recommended first-aid treatment for a burn or scald?	Open-response
When someone has a burn it is recommended that you should apply cold running water. Do you know for how long you should apply cold running water? *NB: this question will be hidden until after the question above is answered*	• 1–5 min • 6–10 min • 11–15 min • 16–19 min • 20 min or more
Secondary outcome measures:	
Frequency of: • App opens • Intervention message views • Pop quiz completions • Photo-sharing	

### Secondary outcome measures

The secondary outcome measures relate to the gamification methods, measuring participants frequency of engagement with the Cool Runnings app (see Table 1).

### Data analysis

All statistical analyses will be conducted using SPSS version 23 (IBM Corporation, Armonk, NY, USA). Descriptive statistics will describe and compare the characteristics of the intervention and control group participants, and pre-knowledge difference. Chi-square analyses will be conducted in order to determine whether there is an increase in the proportion of mothers who can correctly identify the appropriate burn first aid (type and length) (component 1), the main cause of burns/scalds in children under 15 years (component 2), and/or the main age group at risk for burns/scalds (component 3), in the intervention group relative to the control group post intervention.

Increase in knowledge can also be considered a categorical variable (increase versus no increase). Cumulative incidence of increased knowledge in the intervention group versus control group will be calculated, as well as relative risk, absolute risk, absolute risk reduction and numbers-needed-to-treat. This will allow examination of the strength and magnitude of the association between the intervention and change in knowledge.

Where the sample size allows, stratified analyses will be conducted to assess the effect of the intervention in subgroups (age groups; socioeconomic status). In addition, logistic regression will be used to assess increase versus no increase in knowledge of each of the three components of the primary outcome measure. Crude and adjusted analyses will be reported. Methods such as ANCOVA will be used to assess the effect of the intervention while controlling for pre-intervention knowledge, as well a relevant (demographic) confounding factors (this may include, but is not limited to age, socioeconomic status, rurality, education, etc.). Confounding factors will be identified in the descriptive analyses.

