### Sample size

A cross-sectional study of knowledge and attitudes toward burn first aid in Queensland by Cuttle et al. [19] showed that 29 % of mothers of children aged 0–4 years in Brisbane correctly identified appropriate burn first aid (cool running water for 20 min). Assuming 90 % power and alpha = .05, in order to detect a 20 % increase in the proportion of mothers who can correctly identify the appropriate burn first aid (type and length) in the intervention group relative to the control group, 240 participants in total are required (120 each in intervention group and control group), with 95 % confidence. This will allow detection of improvement in the intervention group from 29–49 %, with no improvement in the control group.

In order to determine the proportion of participants who correctly identify the main cause of burns/scalds in children under 15 years, and/or the main age group at risk for burns/scalds, a sample size of 96 is required. This will allow detection of the true proportion in this population with 95 % CI and 10 % precision (assuming 50 % prevalence, the most conservative estimate possible). Further, in order to detect a subsequent increase in knowledge of 20 % on both these dimensions for the intervention group relative to the control group, a total sample size of 240 is required (120 in each group). Assuming 50 % loss to follow-up in each group, a total sample of 480 is required (240 intervention; 240 control).

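### The increase/no-increase variable counts only wrong-to-right answers, so the relative risk and logistic odds ratio built on it measure gain alone and vary with answer turnover

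*Protocol article*

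**What the plan says.** All references are to the protocol article.

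- **Primary outcome measure:** the outcome is change in knowledge, in three components, and "each of these variables is recoded into dichotomous variable (correct/incorrect").
- **Data analysis, main comparison:** "Chi-square analyses will be conducted in order to determine whether there is an increase in the proportion of mothers who can correctly identify" the right answer on each component, comparing intervention with control after the intervention.
- **Data analysis, second paragraph:** "Increase in knowledge can also be considered a categorical variable (increase versus no increase"). Then: "Cumulative incidence of increased knowledge in the intervention group versus control group will be calculated, as well as relative risk, absolute risk", followed by absolute risk reduction and NNT. The stated purpose is "examination of the strength and magnitude of the association between the intervention and change in knowledge".
- **Data analysis, third paragraph:** "logistic regression will be used to assess increase versus no increase in knowledge of each of the three components" of the primary outcome, with crude and adjusted results. Separately, "Methods such as ANCOVA will be used to assess the effect of the intervention while controlling for pre-intervention knowledge" and demographic factors.
- **Sample size:** a cited survey found that "29 % of mothers of children aged 0–4 years in Brisbane correctly identified appropriate burn first aid". The target is 49% in the intervention group with the control group unchanged.

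The section does not restrict the increase variable to mothers who were wrong at baseline. It has no level for going from right to wrong, and it does not say in words how already-correct mothers are coded.

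**The concern.** A mother's pair of answers to a binary item has four possible patterns: wrong–right, right–right, wrong–wrong and right–wrong. A two-level increase variable isolates the first and, read literally, puts the other three together. A mother who kept the right answer is then grouped with one who never had it and one who lost it.

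The article presents the measures computed on this variable as the size of the intervention's effect on change in knowledge. The chi-square yields a p-value, and the only effect measures the article names come from the increase variable. If that variable does not track the proportion who end up correct, the published relative risk, odds ratio and possibly NNT will describe something other than what the chi-square tested, and could disagree with it.

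**Working it through.** **Inputs.** From Sample size: 29% correct at baseline, 29% versus 49% after, 90% power, alpha 0.05 (taken as two-sided), 120 evaluable per group. Gain and loss rates are assumptions throughout, because the article gives none.

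**1. The plan's own figure.** Unpooled two-proportion formula: n = (1.960 + 1.282)² × (0.29×0.71 + 0.49×0.51) / 0.20² = 10.51 × 0.4558 / 0.04 ≈ 119.7, so 120 per group. This reproduces the stated size. It is a calculation for the proportion correct after the intervention, not for the increase variable.

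**2. Identity.** Let b be the baseline proportion correct, and G and L the proportions of all mothers who gain and lose the right answer.

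- Proportion correct at 6 months = b + G − L.
- Proportion with an increase = G, which cannot exceed 1 − b. At 29% baseline the ceiling is 71%: about 0.29 × 120 ≈ 35 mothers per group cannot have the event.
- With equal baselines, difference in 6-month correctness = difference in G − difference in L.

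**3. Same true effect (29% versus 49%), equal losses in both arms.** For 6-month correctness: risk difference 20 points, NNT 5.0, RR 0.49/0.29 = 1.69, OR 2.35.

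| Loss in each arm | Increase, control vs intervention | Risk difference | NNT | RR | OR |
|---|---|---|---|---|---|
| 0 points | 0% vs 20% | 20 points | 5.0 | infinite | infinite |
| 5 points | 5% vs 25% | 20 points | 5.0 | 5.0 | 6.33 |
| 10 points | 10% vs 30% | 20 points | 5.0 | 3.0 | 3.86 |

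The risk difference and NNT are right in every row. The RR and OR change with turnover although the effect on knowledge is identical.

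**4. Losses that differ between arms.** Gain/loss in points, control then intervention; power by simulation at 120 per group.

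| Baseline | Control | Intervention | Correct at 6 months | Increase | Power, correctness | Power, increase |
|---|---|---|---|---|---|---|
| 50% | 15/15 | 25/5 | 50% vs 70%, NNT 5 | 15% vs 25%, NNT 10 | 89% | 50% |
| 50% | 10/10 | 25/5 | 50% vs 70%, NNT 5 | 10% vs 25%, NNT 6.7 | 90% | 88% |
| 29% | 10/10 | 20/20 | 29% vs 29% | 10% vs 20%, RR 2.0 | 5% (false positives) | 59% |

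The first row halves the apparent effect. The third shows a benefit where net knowledge is the same in both arms.

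**5. Power under equal losses.** At 29% baseline with 10/10 versus 30/10, power is 98% for the increase variable and about 89% for correctness. The power comparison can therefore go either way.

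**6. Restricting to mothers wrong at baseline.** RR is unchanged, because both proportions are divided by 1 − b. In the equal-loss table the risk difference becomes 0.20/0.71 = 0.282, so NNT moves from 5.0 to 3.5. At 50% baseline it would be 0.20/0.50 = 0.40, NNT 2.5. Losses remain uncounted.

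**7. Adjusted logistic model.** If baseline correctness enters a model for increase in all mothers, the baseline-correct stratum contains no events. This is separation: the baseline coefficient has no finite estimate, and the arm effect is informed only by mothers wrong at baseline.

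**The case against.** **The trial's powered test is untouched.** This stands. The chi-square compares 6-month proportions, the sample size rests on it, and an analysis controlling for baseline knowledge is planned as well. The increase variable is introduced as an additional way of looking at the data.

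**Randomisation balances already-correct mothers.** This stands in expectation. A reader might infer that NNT on the increase variable is always wrong, but step 3 shows it equals the 6-month NNT whenever losses are equal.

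**The power loss is selective.** This also stands. A reader might take the fall from 89% to about 50% as typical. It arises only under an assumed reduction of loss by the intervention; it almost vanishes in the second row of step 4 and reverses in step 5.

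**Half of mothers cannot have the event on components 2 and 3.** The documents do not support this. The 50% in Sample size is a worst-case value for a precision calculation, not an expected baseline rate.

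**Cumulative incidence may already imply an at-risk denominator.** That is possible, and the coding of already-correct mothers is not stated. That reading would remove the grouping of retained with never-correct knowledge. It would still leave losses uncounted and would change the NNT (step 6).

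**Incidence of gain is a legitimate part of change.** Agreed as a descriptive quantity, but not as the measure of the whole effect on knowledge.

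**Conclusion.** The point holds in a limited form and should be fixed. With binary items, the increase variable registers gain only. Its RR and logistic OR depend on how much answers turn over between questionnaires: infinite, 5.0 or 3.0 against 1.69 for the same 29% versus 49% effect. Its risk difference and NNT are correct when losses are equal in both arms and misleading when they are not, for example NNT 10 instead of 5, or RR 2.0 with no net benefit. Those examples rest on assumed gain and loss rates.

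The defect is confined to the supplementary effect measures and the logistic models. It does not invalidate the primary chi-square, the sample size or the baseline-adjusted analysis. Nor is it a detail left open for an analysis plan: the article itself fixes the variable, the measures computed on it and the model.

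**What to change.** - Make correct at 6 months (yes/no) the outcome of the logistic regression for each component, with arm, baseline correctness of the same item and maternal-age stratum as covariates.
- Derive the risk difference, risk ratio and NNT, with 95% confidence intervals, from that model by standardisation.
- Report transitions by arm as descriptive only: wrong-to-right among mothers incorrect at baseline, and right-to-wrong among mothers correct at baseline.

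The cost is revised analysis wording and a few lines of code. Both questionnaires already supply everything needed, so no new data are required.

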### Randomisation

Randomisation will occur through a simple randomisation table created by computer software (i.e. computerised sequence generation). Randomisation will also be stratified by maternal age (18–28 years; 29+ years), based on mean national maternal age [18].

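### No analysis is named as primary; the test the sample size supports ignores baseline knowledge and the age stratum, and the covariates for adjustment are to be chosen from the trial's own data

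*Protocol article*

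**What the plan says.** The Primary outcome measure section defines the outcome as change in knowledge. It has three components, each scored correct or incorrect and asked both at baseline and at 6 months.

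The Data analysis section lists several between-group analyses and calls none of them primary:

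- First comes a comparison of post-intervention proportions: "Chi-square analyses will be conducted in order to determine whether there is an increase in the proportion of mothers". It has no baseline term and no age term.
- Next come relative risk, absolute risk measures and number needed to treat, with each mother classed as improved or not.
- Subgroup analyses, including by age group, follow if numbers allow.
- Logistic regression is then planned for improved or not on each component, with crude and adjusted results.
- Last is "Methods such as ANCOVA will be used to assess the effect of the intervention while controlling for pre-intervention knowledge", together with demographic factors from an open list in which age is optional. The selection rule is: "Confounding factors will be identified in the descriptive analyses".

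The Randomisation section adds: "Randomisation will also be stratified by maternal age", in two bands (18-28 years; 29 and over).

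The Sample size section works from two simple proportions: "Assuming 90 % power and alpha = .05", with "This will allow detection of improvement in the intervention group from 29–49 %, with no improvement in the control group". It arrives at "240 participants in total are required (120 each in intervention group and control group" and then allows for attrition: "Assuming 50 % loss to follow-up in each group, a total sample of 480 is required (240 intervention; 240 control".

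**The concern.** Three features combine.

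1. The outcome is described as a change and the baseline answer is collected, yet the test that the sample size supports does not use that answer. Nor does it use the factor on which randomisation is stratified. If the baseline answer predicts the 6-month answer, precision that costs nothing is given up.

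2. The adjusted analyses do not clearly repair this. The logistic model's outcome is improvement, so a mother who is right at baseline is a non-event whatever the intervention does. Baseline knowledge is named as something to control for only in the ANCOVA sentence. ANCOVA is a model built for continuous outcomes, and here it is offered as an example rather than as a commitment.

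3. Covariates are to be found by looking at the trial's descriptive results. In a randomised trial, baseline differences between arms arise by chance, so the adjusted estimate depends on which differences happen to appear.

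At stake are some power and, more importantly, certainty about which result answers the trial's question. The chi-square, the logistic model and ANCOVA could disagree, and the article does not say which would prevail.

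**Working it through.** **Step 1: which test does the sample size support?** Inputs from the Sample size section: 29% against 49%, alpha 0.05 (taken as two-sided), 90% power, equal arms. With unpooled variance,

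n per arm = [p1(1-p1) + p2(1-p2)] × (1.960 + 1.282)² / (p2-p1)² = (0.2059 + 0.2499) × 10.51 / 0.04 = 119.8, so 120 per arm and 240 in total.

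This is the article's figure. The pooled version gives 123 per arm (246). A one-sided test (200) and a continuity-corrected test (266) do not fit. For 50% against 70%, the unpooled formula gives 121 per arm (242). Power at 120 per arm is 89.3% for 29% v 49% and 89.0% for 50% v 70%. Attrition: 240 / (1 - 0.5) = 480, as stated. The sample size is therefore that of an unadjusted two-proportion test, which matches the chi-square.

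**Step 2: what does adjustment for baseline add?** The document gives no correlation between the baseline and 6-month answers, so r is an assumption, shown from 0 to 0.5. Simulation: 4,000 trials per setting, 120 per arm, 20-point effect. The adjusted models contain arm, baseline answer and a two-level age stratum. Age had no effect on the outcome, so any gain comes from the baseline answer alone.

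| Control v intervention | r | Power, chi-square | Power, adjusted logistic | Power, linear ANCOVA | Power, unadjusted test of improved or not | Type I error if any of the first three counts |
|---|---|---|---|---|---|---|
| 29% v 49% | 0 | 90.4% | 90.2% | 90.1% | 70.4% | 5.2% |
| 29% v 49% | 0.3 | 90.9% | 93.0% | 93.0% | 75.0% | 6.2% |
| 29% v 49% | 0.5 | 90.2% | 96.0% | 96.0% | 78.6% | 6.9% |
| 50% v 70% | 0 | 89.4% | 89.1% | 89.1% | 38.4% | 4.8% |
| 50% v 70% | 0.3 | 88.5% | 90.8% | 90.7% | 49.5% | 6.4% |
| 50% v 70% | 0.5 | 89.2% | 95.4% | 95.5% | 61.1% | 7.4% |

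Taken singly, chi-square, linear ANCOVA and logistic regression had type I error between 4.3% and 5.6%.

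A separate simulation (8,000 trials) compared chi-square with a Mantel-Haenszel test stratified by baseline answer. From 29%, power was 90% v 92% at r = 0.3 and 90% v 96% at r = 0.5. From 50%, it was 89% v 90% at 0.2, 90% v 93% at 0.4 and 89% v 97% at 0.6.

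As a rough cross-check, the required n scales by 1 - r²: 123 × 0.91 = 112 per arm at r = 0.3, and 123 × 0.75 = 92 at r = 0.5.

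**Step 3: why the improvement outcome is no substitute.** With 29% correct at baseline, 0.29 × 120 = about 35 mothers per arm cannot improve; with 50% it is 60. At r = 0, the proportions improved from a 29% base are 0.71 × 0.29 = 20.6% and 0.71 × 0.49 = 34.8%, so a 20-point effect shrinks to 14.2 points. From 50% they are 0.50 × 0.50 = 25% and 0.50 × 0.70 = 35%, a difference of 10 points. This explains the low power in the sixth column. That column is an unadjusted test; the planned adjusted logistic model of improvement was not simulated.

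**The case against.** The best defence is that the plan is valid and fuller than a quick reading suggests. An unadjusted chi-square is a sound test in a randomised trial and delivers close to the 90% power it was designed for. Adjusted analyses are planned, including a binary-outcome model. Linear ANCOVA on a 0/1 outcome estimates a risk difference, and in Step 2 it gained as much power as logistic regression. The improvement measures use the baseline answer, and age appears as a possible covariate and subgroup. The power gain rests on a correlation the document does not give. The controls' infographic on leading causes of burns could weaken that correlation for component 2. A statistical analysis plan, not shown, may name the final model.

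Most of this stands, and it rules out several stronger readings:

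- *The chi-square or ANCOVA is invalid.* Not supported: each held type I error near 5%.
- *Adjustment is left to ANCOVA alone.* Not so: logistic regression with adjusted results is also planned.
- *Choosing covariates from the data inflates type I error.* Not shown. In a simulation that always adjusted for baseline and added five further covariates only when imbalanced at p < 0.10, type I error was 4-5%. The 6-7% comes from choosing among analyses.
- *Stratification achieves nothing because the table is called simple.* The Randomisation section is ambiguous condensed wording and does not establish this. No gain from adjusting for age was shown either.

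Two things remain. The selection rule is a positive statement in the article, not a detail left for later. And the test that the sample size supports omits a baseline answer that the trial collects.

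**Conclusion.** The point holds as one of efficiency and prespecification. That the chi-square is the main test is an inference from its place in the list and its match with the sample size; the article does not say so.

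For component 1, adjusting for the baseline answer would raise power from about 90% to 92-96% if r is 0.3-0.5, with essentially no gain or loss near 0. For components 2 and 3, at the article's 50% starting value, the corresponding figures are about 89% and 91-95%. If the most favourable of chi-square, ANCOVA and adjusted logistic regression were taken, type I error would be about 6-7% per component for r of 0.3-0.5, and about 5% at r = 0. The article does not say that it would choose in this way; it leaves the choice open.

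These figures assume 120 evaluable mothers per arm, a 20-point effect and the stated range of r. The sample size itself is not in question.

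**What to change.** For each component, name one deciding analysis: a model of the 6-month answer (correct or incorrect) on arm, the baseline answer to the same item, and maternal-age stratum (18-28; 29+). Logistic regression reported as a standardised risk difference with 95% CI would serve. A Mantel-Haenszel analysis over the same strata is a close alternative, but not an equivalent, since it is a different test with a different estimand.

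Delete the sentence "Confounding factors will be identified in the descriptive analyses". List any further covariates, such as education or area of residence, before outcome data are seen, and use the baseline table for description only. Replace the open-ended ANCOVA sentence with the named model. Keep the unadjusted chi-square as supportive, and label the improvement analyses as secondary.

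The cost is wording only: the baseline answers, maternal age and demographic items are already collected, and the sample size need not change. The Trial status section describes the trial period as active, so the change should be dated before the 6-month answers are analysed.
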